#### RQ2: feedback evaluation

4.2.3

Quantitative data from the feedback questionnaire will be analyzed descriptively (means, standard deviations, medians, and ranges). Open-ended responses will be explored using text-mining techniques (e.g., n-gram analysis) to identify commonly used words and phrases. Additionally, the open-ended responses and focus groups will be analyzed using Mayring’s Qualitative Content Analysis [68] with deductive and inductive category development. Categories will be predefined using the interview guideline and enriched with emerging topings from the discussions.

#### RQ3: compliance and self-control analysis

4.2.4

Compliance will be defined as daily completion of both the journal and questionnaire (0 = not completed, 1 = completed) across the 14-day study period. Daily compliance will be analyzed using a mixed-effects logistic regression with fixed effects for group, day, trait self-control (SCS-K-D), mean state self-control (SSCCS), their relevant interactions, and a random intercept for participants to account for repeated measures. Spearman’s rank correlation will be used descriptively to assess the association between trait self-control and total journals completed.

To predict on a global level whether participants will drop out (0) or complete the study (1), a logistic regression will be performed with trait self-control (SCS-K-D) and mean state self-control (SSCCS) as predictors of study completion. The study will be considered completed if participants submit the feedback questionnaire at the end of the study.

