## Research questions and hypotheses

2

Building upon the illustrated gaps in current research, this study investigates the potential of NLP applied to digital journaling data with the aim of monitoring and supporting students’ emotional well-being, while generating individualized feedback on the journaling content and evaluating the students’ preferences.

Primarily, we hypothesize that (RQ1) emotional well-being and stress levels can be predicted from journaling entries using NLP. Prediction accuracy is expected to be higher for spoken entries (transcribed speech) compared to typed entries. Secondly, we hypothesize that (RQ2) the participants will evaluate the individualized feedback positively, indicating its acceptability and potential to foster reflection and compliance. Thirdly, we expect (RQ3) higher *state self-control* and *trait self-control* to be associated with greater adherence to the study protocol, and will be negatively correlated with dropout rates.

Furthermore, we will undergo (RQ4) an exploratory analysis of the improvement of the students’ emotional well-being over the study period, including the difference when typing vs. speaking the journal entries. Lastly, (RQ5) the predictive performance of NLP models will be compared to that of human experts (psychotherapists and clinical psychologists) in an exploratory manner to gain a practical perspective on the models’ performance. If RQ1 and RQ2 should hold true, future work should proceed to explore the usage of NLP to provide feedback automatically.

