#### RQ4: exploratory analysis of well-being

4.2.5

To explore whether emotional well-being and stress change over the 14-day study period and whether these changes differ between the type and speak groups, a mixed-effects model will be used. Fixed effects will include group, day, and their interaction (Day × Group). Random intercepts and slopes for participants will account for within-subject variability and individual trajectories.

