#### Handling of missing data and dropout

4.3.1

Incomplete daily records will not be used for analysis. Specifically, if a participant provides only a journal entry or only a daily questionnaire for a given day, that day’s data point will be excluded from the dataset. Missing data will not be imputed, as journal entries and subjective reports cannot be reliably reconstructed. Instead, the extent and patterns of missingness will be explored descriptively to assess whether data are missing at random or show systematic trends (e.g., participant characteristics, or study phase). Participant dropout will be recorded, including the timing and, where possible, reasons for discontinuation. Dropout has been accounted for in the sample size calculation.

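### RQ3 daily compliance has no end at withdrawal, so days after leaving count as non-compliance; tests of interactions with day are then too liberal, and a self-control effect on dropout can pass for an effect on adherence

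*Protocol article*

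**What the plan says.** All references are to the protocol article.

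- **Outcome (4.2.4).** Compliance is "daily completion of both the journal and questionnaire (0 = not completed, 1 = completed) across the 14-day study period". No rule ends the series when a participant leaves.
- **Model (4.2.4).** A "mixed-effects logistic regression with fixed effects for group, day, trait self-control (SCS-K-D), mean state self-control (SSCCS), their relevant interactions", with "a random intercept for participants to account for repeated measures".
- **Separate dropout analysis (4.2.4).** At participant level, "a logistic regression will be performed with trait self-control (SCS-K-D) and mean state self-control (SSCCS) as predictors of study completion". Completion has its own definition: "The study will be considered completed if participants submit the feedback questionnaire at the end of the study".
- **Hypothesis (section 2).** Higher state and trait self-control are expected "to be associated with greater adherence to the study protocol, and will be negatively correlated with dropout rates". Adherence and dropout are thus two outcomes.
- **Missing data (4.3.1).** A day with only a journal or only a questionnaire is excluded. "Participant dropout will be recorded, including the timing and, where possible, reasons for discontinuation".
- **Contrast with RQ4 (4.2.5).** There, "Random intercepts and slopes for participants will account for within-subject variability and individual trajectories". RQ3 has no such slope.

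**The concern.** A student who leaves on day 3 and a student who stays but skips evenings both produce zeros, but of different kinds. Leaving gives an unbroken run of zeros to day 14. A random intercept only shifts a participant's level up or down; it cannot represent a switch from mostly ones to all zeros. Standard errors for terms that vary with day are then too small.

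Two consequences follow for RQ3. First, day-by-group and trait-by-day, both covered by the unspecified interactions in 4.2.4, may be declared significant too often. Second, if self-control affects only whether students leave, the daily model can report that it affects daily adherence. The two parts of the hypothesis would then look separately supported when only one is.

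**Working it through.** **The plan's own figure (4.1).** N = D / (d × (1 − r)) = 500 / (14 × 0.72) = 49.6, so 50 per group and 100 in total. This reproduces.

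**How many zeros come from leaving.** From the protocol: 28% dropout, 14 days. Assumed: the last active day is spread evenly over days 1 to 13, so a dropout loses 7 days on average. Post-dropout days are then 0.28 × 7/14 = 14% of person-days. Divided by the share of all person-days scored 0:

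- overall completion 60%: 0.14 / 0.40 = 35%;
- overall completion 70%: 0.14 / 0.30 = 47% (simulated: 46%);
- overall completion 79%: 0.14 / 0.21 = 67% (simulated: 65%).

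**Type I error.** Simulated trials had 50 + 50 participants over 14 days. In-study completion was constant over time, with no group or trait effect and the same dropout in both groups. The fitted model was a random-intercept logistic regression with group, day, day-by-group and trait. Assumed: random-intercept SD 1, plus the completion levels and dropout timings in the table. There were 500 replicates per row with two-sided tests at 5%, so the Monte Carlo standard error at 5% is √(0.05 × 0.95 / 500) = 1.0 point.

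| Dropout and timing | Median in-study completion | Zeros after leaving | Day | Day-by-group | Group | Trait |
|---|---|---|---|---|---|---|
| 28%, even | 73% | 35% | 91.2% | 12.4% | 5.2% | 6.0% |
| 28%, even | 85% | 46% | 97.8% | 16.2% | 5.2% | 5.0% |
| 28%, even | 94% | 65% | 99.6% | 18.2% | 4.8% | 5.6% |
| 28%, early (last active day 1 to 4) | 85% | 61% | 93.8% | 14.6% | 5.6% | 4.8% |
| 14%, even | 85% | 28% | 66.4% | 12.8% | 4.2% | 6.0% |
| None | 85% | 0% | 5.6% | 5.6% | 5.4% | 6.8% |
| 28%, even, days after leaving removed | 85% | n/a | 5.0% | 5.6% | 4.8% | 6.4% |

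With trait-by-day added (400 replicates, second-row setting), that term rejects in 17.2% with post-dropout zeros and 5.8% without them. At 92% completion and SD 0.8 (300 replicates), day-by-group rejects in 21.7% and trait-by-day in 19.7%; with those days removed, 8.3% and 4.0%. A small run of 150 replicates at about 90% completion gave 26% for day-by-group, with a Monte Carlo standard error of √(0.26 × 0.74 / 150) = 3.6 points.

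**Self-control acting on dropout only.** Assumed odds ratio 2 per SD of trait, with no effect on in-study completion:

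| Coding | Trait rejects | Trait-by-day rejects |
|---|---|---|
| Post-dropout days scored 0 (85% completion; two sets of runs) | 41% and 49% | 74% and 67% |
| Post-dropout days scored 0 (92% completion) | 57% | 75% |
| Days after leaving removed (85% and 92%) | 5.7% and 6.0% | 7.3% and 5.7% |

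**Candidate remedies** (28% dropout spread evenly, 90% active completion, both timing and completion assumed):

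- As written: day-by-group 21%, trait-by-day 17%.
- Days after leaving removed: 6% and 6%.
- Random slope for day alone: day-by-group still 13%.
- All 14 days with participant-clustered robust errors: 6% and 5%.
- Follow-up cut at last activity for everyone without a formal opt-out: spurious day effect in 30% of runs; 4% when the cut is limited to recorded dropouts.

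The models behind these rates omit mean state self-control, which 4.2.4 includes.

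**The case against.** The strongest points on the other side, and what stands of each:

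- **The zero coding is inferred.** True: 4.2.4 never expressly says that days after withdrawal score 0. But the definition covers all 14 days. The exclusion in 4.3.1 concerns days with one component, and a day after leaving has neither. Excluding every uncompleted day would leave no zeros to model.
- **The problem depends on when students leave.** This stands. The sample-size formula treats the 28% as contributing nothing, and section 5 mentions dropout before the study begins. Someone with no completed day has no mean state self-control and falls out of the model. With all dropout before day 1 and those participants excluded, day rejected in 4.7% and day-by-group in 4.0% of simulated trials.
- **The interactions are not named, and RQ3 states no group or day hypothesis for adherence.** Also true. However, the relevant interactions follow a list containing group, day and trait, and the self-control hypothesis itself is exposed when self-control drives dropout.
- **All-participant completion is a legitimate meaning of adherence.** It is. A reader might infer that the day test is invalid because it rejects in nearly every run. The protocol does not support that: completion among all participants really does fall when students leave. The question is what the day coefficient means.
- **The daily analysis is not simply the dropout analysis again.** A reader might infer that it largely is. Post-dropout zeros run from 28% to 65% of all zeros, depending on assumed completion, dropout rate and timing. Completion is also defined by the feedback questionnaire, so a student with 14 completed days can still count as a dropout. The overlap is real but partial.

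**Conclusion.** The concern holds in a limited form. On the definition in 4.2.4, days after leaving count as non-compliance in a model that cannot represent them. With the protocol's 28% dropout spread over the two weeks, day-by-group and trait-by-day tests run at roughly 12% to 22% instead of 5%. The day effect combines withdrawal and in-study decline. A self-control effect on dropout alone (assumed odds ratio 2 per SD) is reported as a trait effect on daily adherence in 41% to 57% of simulated trials.

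It does not follow that every RQ3 test fails. Group and trait main-effect tests stay near nominal (4% to 9% over all runs) when trait has no effect. The size of the problem rests on dropout timing, in-study completion and between-participant spread, none of which the protocol gives. RQ1 and RQ2 are unaffected. The change is worth making because RQ3 is a stated hypothesis and dropout timing is already to be recorded.

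**What to change.** In 4.2.4:

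1. Analyse daily compliance on days at risk. End follow-up only for participants recorded as dropouts, at the time recorded under 4.3.1. Use last activity only where such a dropout has no recorded date. An unsubmitted feedback questionnaire alone should not shorten the series.
2. Keep all 14 days, including trailing missed days, for everyone else. Do not apply a last-activity cut-off to all participants: it deletes final missed days and creates a false upward trend. Section 3.3 also provides for reminders after missed days, so silence is not necessarily leaving.
3. Report the all-14-days version as total protocol completion, using participant-clustered robust standard errors or a participant bootstrap for terms involving day. Do not rely on a random slope alone.
4. Name the interactions to be fitted, and reconcile with 4.3.1 whether a day with only one component scores 0 or is excluded.

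The cost is analysis wording; no new data are needed. The downside is that a few dropout dates must be inferred, and at-risk compliance is conditional on remaining in the study and must be described so.

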#### Daily target variables

3.4.3

The daily surveys will include the Multidimensional Mood State Questionnaire (MDBF), a parsimonious six-item mood scale designed for momentary assessment in daily life to evaluate participants’ well-being [53]. This instrument is derived from the German-language Multidimensional Mood Questionnaire (MDMQ) [54] and captures three dimensions: valence (good–bad mood), arousal (wakefulness–fatigue), and calmness (calmness–restlessness). Scores range from 1 (bad mood, fatigue, restlessness) to 7 (good mood, wakefulness, calmness). In addition, the ecological momentary assessment version of the Perceived Stress Scale-4 (PSS-4) [55] will be administered to assess daily stress levels. Both the MDBF and the PSS-4 will be adapted to refer to the entire past day rather than the immediate moment of completion. This adaptation will ensure consistency with the journaling entries, which also cover the whole day, thereby enabling the questionnaire scores to be meaningfully predicted from the entries by the NLP models. Furthermore, participants will answer two questions from the State Self-Control Capacity Scale (SSCCS) [56] to assess their situational self-control when journaling.^4^ Finally, participants will also select from a predefined list the topics mentioned in their journal entry. The possible topics are adopted from a North American study on diary content [57] and translated into German: movement, family, food, friends, religion/spirituality, health, love, recreation, school, sleep, and work. The term “religion/spirituality” will be used instead of “god,” as religion is practiced less centrally in European countries compared to North America [58].

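### RQ3 predicts compliance and completion from mean state self-control, which is observed only on compliant days, so the state result is hard to interpret

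*Protocol article*

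**What the plan says.** All references are to the protocol article.

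- Section 2 (RQ3) expects higher state and trait self-control "to be associated with greater adherence to the study protocol, and will be negatively correlated with dropout rates".
- Section 3.4.3 places state self-control in the daily survey: "participants will answer two questions from the State Self-Control Capacity Scale (SSCCS) [56] to assess their situational self-control when journaling". Section 3.3 puts that survey directly after the journal entry. Section 3.4.1 measures only trait self-control (SCS-K-D) at baseline.
- Section 4.2.4 defines the first outcome: "Compliance will be defined as daily completion of both the journal and questionnaire", scored 0 or 1 per day. Its model has "fixed effects for group, day, trait self-control (SCS-K-D), mean state self-control (SSCCS), their relevant interactions, and a random intercept for participants".
- For the second outcome, "a logistic regression will be performed with trait self-control (SCS-K-D) and mean state self-control (SSCCS) as predictors of study completion". Completion has its own definition: "The study will be considered completed if participants submit the feedback questionnaire at the end of the study".
- Section 4.3.1 excludes a day's data point "if a participant provides only a journal entry or only a daily questionnaire for a given day", and adds: "Missing data will not be imputed, as journal entries and subjective reports cannot be reliably reconstructed".

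The article gives no lagged, early-window or baseline version of state self-control, and no rule for a participant without any SSCCS value.

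**The concern.** The predictor can be seen only where the daily outcome equals 1. Four consequences follow.

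1. A participant with no complete day has no mean. A complete-case fit drops that person from both models, including from the estimate of the trait effect.
2. Someone who stops the diary early has a mean over early days, while someone who continues has a mean over the whole period. Any drift of SSCCS over the two weeks then looks like an association with adherence.
3. If low-control days are the skipped days, which is one way for the RQ3 hypothesis to be true, the means of poor compliers are pushed up and the association shrinks.
4. A 14-day mean uses later days to explain compliance on earlier ones.

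At stake is the state self-control half of a directional hypothesis: neither a positive nor a null result could be read with confidence.

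**Working it through.** **The plan's own figure.** Section 4.1: N = D / (d × (1 − r)) = 500 / (14 × 0.72) = 500 / 10.08 = 49.6, rounded to 50 per group, 100 in total. This reproduces and is not in dispute. It gives the setting: 100 participants, 14 days, 28 expected dropouts.

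**Step 1. Which days enter the mean** (sections 3.3, 3.4.3, 4.2.4 and 4.3.1 together):

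| Day | Compliance | SSCCS answered | Enters the mean under 4.3.1 |
|---|---|---|---|
| Journal and questionnaire | 1 | yes | yes |
| Questionnaire only | 0 | yes | no |
| Journal only | 0 | no | no |
| Neither | 0 | no | no |

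Under the plan's exclusion rule the mean is taken only over days with compliance 1.

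**Step 2. Who has no mean.** Let f be the share of the 28 dropouts with no complete day. The article does not give f, so a range is shown. Participants kept = 100 − 28f, dropouts kept = 28(1 − f), apparent completion = 72 / (100 − 28f).

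| f (assumed) | Participants kept | Dropouts kept | Apparent completion |
|---|---|---|---|
| 0 | 100 | 28 | 72% |
| 10% | 97 | 25 | 74% |
| 25% | 93 | 21 | 77% |
| 50% | 86 | 14 | 84% |

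**Step 3. How drift produces an association.** Someone who completes days 1 to 4 and then stops is averaged around day 2.5; someone who completes all 14 is averaged around day 7.5. At an assumed drift of 0.05 SD per day their means differ by 5 × 0.05 = 0.25 SD with no true relation. Over the whole diary this drift amounts to 13 × 0.05 = 0.65 SD.

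**Step 4. False-positive rate with no true effect** (simulation, 100 participants, 14 days, nominal 5%).

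- *Completion model, 1,500 replicates.* Person SD 1, day SD 1, dropout logit −1.0 (about 27%), mean SSCCS as sole predictor. No drift: 4.6%. Drift ±0.05 per day: slope −0.16 or +0.15 instead of 0, rejection 10–12%. Drift −0.1: slope −0.30, rejection 27%, against 4.5% with a fully observed 14-day mean.
- *Both models, 300 replicates.* Person variance 0.4, autocorrelated day variance 0.6, stopping hazard 0.025 per day (1 − 0.975^14 = 30%). No drift: 5.7% (compliance) and 4.3% (dropout). Drift 0.03: 10% in both. Drift 0.05: 15–17% and 18%. Monte Carlo error is about 2–3 points.
- *A further simulation of the same size*, drift 0.05: 17–21% across the two models, about 5% without drift.

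The first setup has total SD √(1 + 1) = 1.41, so its drift of 0.05 is 0.05 / 1.41 = 0.035 of a total SD. That largely explains why its 10–12% sits beside the 10% found at 0.03 in the second.

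**Step 5. Attenuation with a true person-level effect of 0.5** (first setup, 25% of dropouts with no complete day; a person-level binomial regression stands in for the compliance model, and only its slopes are used).

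| Day-level effect | Slope, full 14-day mean | Slope, compliant days only |
|---|---|---|
| 0 | 0.47 | 0.41 |
| 0.5 | 0.49 | 0.39 |
| 1 | 0.48 | 0.35 |

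Some shrinkage occurs without day-level selection, because short means are noisy and non-starters are lost; selection adds to it. In the completion model, power falls from 53% to 38% (f = 25%) and to 27% (f = 50%).

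**The case against.** The best counter-argument is that the harm is conditional and the setting modest. RQ3 is third-ranked, worded as association, and carries no decision rule; section 3.1 calls the whole approach exploratory; the sample size rests on RQ1. This stands and limits the severity. It does not remove the point: section 2 states RQ3 as a directional hypothesis and reserves the exploratory label for RQ4 and RQ5.

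Several stronger readings are tempting, and the documents do not support them.

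- *The predictor is a function of the outcome, so a false positive is automatic.* It is selected by the outcome, not computed from it. Without drift or day-level selection the error rate is about 5%. The article reports no drift in SSCCS; it only allows that journaling may change well-being and stress (section 5).
- *SSCCS is missing on every day coded 0.* A questionnaire-only day is coded 0 and does yield a score. It is lost through section 4.3.1, whose application to this mean is not spelled out; applied literally to the compliance outcome it would also delete partly completed days coded 0.
- *Dropouts have early means and completers have 14 days.* Completion means submitting the feedback questionnaire, not continuing the diary. When completion was made independent of diary stopping for half the participants, false positives at 0.05 SD per day fell from about 20% to 9%.
- *All early dropouts are lost.* Only those with no complete day are, about 3% of participants in one simulation. The larger losses in step 2 need f of 25–50%.
- *The mean discards most of the power.* For a purely day-to-day effect, power was 8% with the observed mean and 63% with a lagged value, but a fully observed 14-day mean reached only about 12%. That contrast is between two estimands and does not measure harm from missing days.

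It could also be said that the mixed model handles missingness. A random intercept copes with unbalanced outcomes, not with a covariate that is undefined or selected by the outcome.

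**Conclusion.** The point holds in a limited form. From the document alone, mean SSCCS covers only compliant days under the exclusion rule, over a number and timing of days set by the outcome, and is undefined for participants with no complete day. This follows from what section 4.2.4 fixes; it is not a detail left to a statistical analysis plan.

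The size rests on assumptions. At a drift of 0.05 SD per day and no true effect, about 10–21% of tests are falsely positive, about 9% where completion is loosely tied to diary stopping, and about 5% without drift. Day-level selection attenuates a true association. The direction of the net bias cannot be known beforehand. The simulations approximate the planned models: the compliance tests used participant-clustered logistic regression or a person-level stand-in.

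A reader might infer that RQ3 as a whole fails. It does not: the Spearman correlation of trait self-control with journals completed needs no SSCCS and keeps everyone, and RQ1 and RQ2 are untouched. Severity: should fix.

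**What to change.** Amend section 4.2.4 before analysis:

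1. Fit the completion and compliance models with SCS-K-D, plus group and day where planned, on all randomised participants and without SSCCS.
2. Test state self-control on completion in a separate landmark model: SSCCS from the first completed day, adjusted for which day that was, counting only later non-completion. In simulation with drift 0.05 this held 4–5% false positives.
3. In the daily compliance model, replace the mean with SSCCS from the last completed day before day t, with day as a covariate, restricted to days up to permanent discontinuation. The restriction is essential. Carrying the last value past a permanent stop still gave about 11.5–14% false positives; with the restriction, 5–6% in one simulation and 8% in another. The rule for dating discontinuation must be written down; section 4.3.1 already plans to record its timing.
4. Report the number of participants with no complete day, by group.

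The cost is revised wording and some extra analysis, with no new data. The landmark model has less power, person-days before the first completed entry have no lagged value (in one simulation about 12–13% of person-days had none), and participants who never start appear only in the trait models.

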### Participants and recruitment

3.2

Eligible participants will be university students who (a) are at least 18 years of age, (b) possess an internet-enabled smartphone (iOS or Android), and (c) demonstrate adequate proficiency in German, defined as fluent comprehension and production in both spoken and written form. Exclusion criteria are intentionally kept to a minimum to promote broad accessibility. Participants will be excluded only if they are experiencing an acute mental health crisis that necessitates immediate clinical intervention (e.g., acute suicidality).

To minimize participant attrition, several incentive mechanisms will be implemented: (1) all participants will receive individualized feedback upon completion of the 14-day study period; (2) participants who successfully complete the study will be compensated with a €10 voucher redeemable at various online retailers; (3) three additional €50 vouchers will be allocated by lottery among participants within the upper 50% of compliance; and (4) psychology and cognitive science students at the University of Tuebingen will be eligible to obtain university-internal credits.

A non-probability convenience sampling strategy is applied. Recruitment will be carried out through several complementary channels. Primary outreach will occur via university-wide email distribution lists at the University of Tuebingen, where psychology and cognitive science students will be explicitly informed that participation qualifies for university-internal credits. Students from all other disciplines will likewise be eligible and encouraged to participate. Additional on-campus recruitment will be conducted through the display of posters in university buildings. Digital recruitment will include dissemination of study information via the official social media account of the University Hospital Tuebingen and the extension of outreach to students at other universities through targeted posts in messenger-based student groups.

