#### Baseline survey

3.4.1

Prior to the start of the study, participants will complete several baseline questionnaires: a demographic questionnaire capturing medication use and health history (see Additional file 1 of the Supplementary Material to this article), an educational level questionnaire based on the International Standard Classification of Education—Fields of Education and Training 2013 [49], and the WHO-5 Well-Being Index (WHO-5) [50] assessing general well-being. In addition, mental health and stress will be evaluated using the 21-item Depression Anxiety Stress Scales (DASS-21) [51], while dispositional self-control will be measured with the Brief Self-Control Scale (SCS-K-D) [52]. All instruments were administered in their validated German versions.

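### The RQ3 models carry no term for a course-credit incentive open to only some participants, which costs the daily compliance model some power and leaves both models open to confounding

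*Protocol article*

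**What the plan says.** Section 3.2 (Participants and recruitment) introduces the incentives by their purpose: "To minimize participant attrition, several incentive mechanisms will be implemented". There are four. Individual feedback, the €10 voucher and the €50 lottery are open to all who meet a participation condition. The fourth is restricted: "psychology and cognitive science students at the University of Tuebingen will be eligible to obtain university-internal credits". The same section opens the study to students who cannot earn credits: "Students from all other disciplines will likewise be eligible and encouraged to participate", and it plans "the extension of outreach to students at other universities through targeted posts in messenger-based student groups".

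Section 4.2.4 (RQ3) names the terms of both models. Daily compliance is to be modelled by mixed-effects logistic regression, and the terms listed are these: "fixed effects for group, day, trait self-control (SCS-K-D), mean state self-control (SSCCS), their relevant interactions, and a random intercept for participants". For completing the study or dropping out, "a logistic regression will be performed with trait self-control (SCS-K-D) and mean state self-control (SSCCS) as predictors of study completion". Neither list has a term for credits, field of study or university.

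Section 3.4.1 (Baseline survey) includes "an educational level questionnaire based on the International Standard Classification of Education—Fields of Education and Training 2013". It does not say that the university attended is recorded.

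**The concern.** By the protocol's own account the incentives are there to influence whether people stay in the study, and staying in is what RQ3 models. One incentive reaches only part of the sample, so participants fall into two reward strata. Self-control is measured and not randomised, so assignment to typing or speaking does nothing to balance incentive access across levels of self-control.

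Two consequences are possible. First, in the random-intercept model, variation between people that is due to credits is left in the between-person term and makes the self-control effect harder to detect. Second, if credit-eligible students differ from the others in self-control, part of the credit effect is reported as a self-control effect, in either direction. Section 2 states RQ3 as a directional hypothesis, so both the estimate and its power matter.

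**Working it through.** **Inputs from the protocol.** Section 4.1: 500 data points per group, 14 days, 28% dropout, 50 participants per group. The stated size reproduces: 500 / (14 × 0.72) = 49.6, rounded up to 50 per group, 100 in total.

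**Assumptions (the documents give none of these).** The share of credit-eligible students, the credit odds ratio, the between-person variance on the logit scale, the true self-control effect, and any self-control difference between strata. I also assume that the 28% applies to completion as RQ3 defines it. Mean state self-control was left out of the simulations for simplicity.

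**Daily compliance model: standard error.** With self-control unrelated to eligibility, an approximate between-person standard error for a one-SD change in self-control is

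- with the credit term: √[(τ² + e) / 100], where e = 1 / [14 p (1 − p)]
- without it: √[(τ² + e + x) / 100], where x = q(1 − q)(ln OR)²

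Here τ² is the random-intercept variance, p the daily compliance and q the eligible share. With p = 0.72, e = 1 / (14 × 0.72 × 0.28) = 0.354.

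| τ² | q | Credit OR | x | SE with term | SE without | Ratio |
|---|---|---|---|---|---|---|
| 2 | 0.3 | 2 | 0.101 | 0.153 | 0.157 | 1.02 |
| 1 | 0.5 | 2 | 0.120 | 0.116 | 0.121 | 1.04 |
| 2 | 0.3 | 4 | 0.404 | 0.153 | 0.166 | 1.08 |
| 1 | 0.5 | 4 | 0.480 | 0.116 | 0.135 | 1.16 |

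The inflation is thus about 2 to 4% at odds ratio 2 and 8 to 16% at odds ratio 4. At the simulation settings used next (τ² = 1.2² = 1.44, q = 0.4) the same formula gives 3%, 8% and 16% for odds ratios 2, 3 and 5.

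**Daily compliance model: power.** Simulation with 100 participants, 14 days, 40% eligible, random-intercept SD 1.2, self-control log-odds 0.35 per SD and no self-control difference between strata. The person-level fits are binomial logistic regressions with robust standard errors. A second simulation fitted the random-intercept logistic model itself, with the same eligible share and intercept SD.

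| Credit OR | Person-level fits: without → with term | Random-intercept fits: without → with term |
|---|---|---|
| 2 | 68% → 70% | 68% → 71% |
| 3 | 64% → 70% | 66% → 71% |
| 5 | 60% → 72% | 62% → 74% |

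The two agree: a gain of 2 to 3 points at odds ratio 2, and 12 points at odds ratio 5.

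**Completion regression: precision.** Simulation with n = 100, 72% completion, eligible share 30% or 50%, credit odds ratio 2 or 4, and self-control odds ratio 1.0 or 1.5 per SD. Over all scenarios the standard error of the self-control log odds ratio is 0.225 to 0.245 without the credit term and 0.236 to 0.260 with it. Omission does not widen it. With no self-control difference between strata, a true odds ratio of 1.50 becomes 1.44 to 1.49, and power is 35 to 38% without the term against 38 to 40% with it.

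**Completion regression: confounding.** If eligible students score 0.3 to 0.5 SD higher on self-control, a true odds ratio of 1.00 appears as 1.04 to 1.17. The false-positive rate is then about 4 to 10%, against about 4 to 6% with the term. A true 1.50 appears as 1.56 to 1.69. A difference in the other direction would push the estimate down.

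**Daily model: confounding.** With a 0.4 SD difference and credit odds ratio 3, the person-level fits without the term give a slope of about 0.35 or 0.19, depending on direction, against 0.28 with no distortion. (On this scale the simulated 0.35 shrinks to 0.28, so these values show the direction and rough size of the shift, not the bias in the planned mixed model.) With no true effect, the false-positive rate is about 11 to 12%, against about 6% adjusted.

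**Events per predictor.** 28% of 100 gives 28 dropouts: 28 / 2 = 14 per predictor as planned, 28 / 3 = 9.3 with a credit term.

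**The case against.** The strongest reply is that RQ3 asks about association: section 2 expects self-control to be associated with adherence, section 4.2.4 words the dropout model as prediction, and section 3.1 calls the study's approach exploratory. An unadjusted association answers that question, and credit access is one of several characteristics left out. This has weight and keeps the point modest. It does not remove it, because section 2 labels only RQ4 and RQ5 as exploratory and gives RQ3 a direction, and because credits are a feature of the design that the protocol itself aims at the outcome.

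Section 4.3.1 will describe missingness by participant characteristics and record reasons for discontinuation. That could reveal an eligibility pattern but does not adjust for it.

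Three stronger readings are tempting, and the documents do not support them:

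- **That both models lose precision.** The completion regression does not; its standard error is slightly smaller without the term.
- **That the self-control association is confounded.** This needs a self-control difference by eligibility, and no section says there is one.
- **That the field-of-study data already identify who is eligible.** Eligibility also requires enrolment at the University of Tuebingen, and recording of the university is not stated.

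It also stands that at a credit odds ratio of 2 the power gain is only 2 to 3 points.

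**Conclusion.** The point holds in a limited form. Both RQ3 models omit an incentive that the protocol restricts to some participants and directs at attrition. Because section 4.2.4 lists the model terms, this is a stated choice and not a detail left to another document.

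In the daily compliance model the cost is small to moderate: a standard error roughly 2 to 16% larger and power about 2 to 12 points lower, for assumed credit odds ratios of 2 to 5. In the completion regression the cost, absent confounding, is a slight shift of the odds ratio towards 1. In both, confounding is a possibility whose size rests on an assumed self-control difference. If credits do not affect compliance, there is nothing to gain. The sample size is unaffected.

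**What to change.** In section 4.2.4, add a credit-eligibility indicator (yes/no) as a fixed effect in the daily compliance model. Define it from field of study together with enrolment at the University of Tuebingen, recorded at registration or in the baseline survey. Do not define it by whether credits were later claimed, since claiming may itself depend on taking part.

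For the completion regression, keep the planned model and report the credit-adjusted version beside it as a pre-specified sensitivity analysis. With about 28 dropouts expected, making the adjusted version the main result is not clearly better.

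The cost is one sentence, one extra parameter in the daily model, one baseline item if the university is not already recorded, and about 9 instead of 14 dropouts per predictor in the completion sensitivity model. Fixing this before the data are seen keeps the adjustment from looking data-driven.
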